#### Machine learning model establishment, evaluation, and interpretation

Both linear and non-linear machine learning models will be applied to the sets, which include logistic regression, RF, support vector machine, gradient boosting tree (such as XGBoost, LightGBM, Adaboost, and Catboost), and attentive interpretable tabular learning (TabNet). The prediction performance of all models will be evaluated through five measures (area under the receiver operating characteristics [AUROC] curve, precision, recall, F1 score, and accuracy). The acceptably performing machine learning models will be selected according to AUROC. Next, we will calculate the importance scores of the features using the above-chosen algorithms. Features with higher importance scores are more closely related to the accurate prediction of NOAC inappropriate use. Finally, features ranked in the top 50% based on normalized importance scores in selected models will be determined as major predictors and depicted in radar plots.

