#### Data separation and feature filtering

In this process, the data will be randomly divided into training and test sets in a ratio of 8:2, which will be used for the model establishment and verification, respectively. Feature selection will be performed using the Sequence Forward Selection algorithm based on RF. For each group, the algorithm will search from the empty set and subsequently add one variable to the feature subset each time to achieve an optimal performance, which is measured by the F1 score.

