### Statistical analyses

Categorical data will be presented as frequencies and be compared by Chi-squared or Fisher's exact test as appropriate. Continuous data will be reported as mean ± standard deviation or median and interquartile range (IQR) and analyzed by either Student's *t*-test or the Mann–Whitney *U* test. In this study, data will be extracted and summarized using Excel 2016. Univariate and multivariate logistic regression analyses will be applied to ascertain the correlation between candidate variables and NOAC inappropriate use. Multicollinearity between the variables will be shifted based on the variance inflation factor (VIF; VIF > 5 is considered strong collinearity) (25). Two criteria will be considered necessary for a variable to be incorporated into the final prediction model: (a) a univariate *p-*value indicative of NOAC prescription inappropriateness ≤0.05 and (b) a plausible connection with risk factors from NOAC inappropriate prescriptions based on previously published research. The risk tendency of inappropriate NOAC use among risk stratifications will be evaluated by the Cochran-Armitage trend test (26). Machine learning algorithms will be built based on the Scikit-learn package (version 0.22.2). Interaction analyses will be used to compare predictive performance between machine learning models. Statistics will be performed employing STATA software (version 12.0, Stata Corporation LLC, College Station, United States), and a *p* < 0.05 will be considered to be statistically significant.

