Previous studies report relevant risk factors for inappropriate NOACs use. In the SAGE-AF (Systematic Assessment of Geriatric Elements in Atrial Fibrillation) cohort, a potentially inappropriate NOAC dose was prescribed to nearly a quarter of older adults. This stemmed from patients being older, having poor renal function, and higher CHA_2_DS_2_-VASc scores (16). Another Korean study found that NOAC label adherence was approximately 60%, and the risk factors of NOAC under-dosing were independently related to old age (≥75 years), female sex, lower body weight (< 60 kg), renal impairment (CrCl < 50 ml/min), hypertension, previous stroke/transient ischemic attack (TIA)/thromboembolic events, bleeding history, and concomitant dronedarone or antiplatelet agent use (29). In the ORBIT-AF II registry (18), compared with those whose NOAC dose was appropriately reduced, patients accepting inappropriate dose reductions were younger and had lower bleeding risk scores. Physician assessment may have a strong impact on inappropriate NOAC dosing; however, there may also be drug-specific factors. In Mainland China, information on practice patterns of NOAC administration and the use of NOACs for licensed indications in older patients remains scarce.

Currently, few studies have focused attention on the prediction model of the risk factors of NOAC inappropriateness in elderly patients with AF. Considering that inappropriate NOACs doses are prescribed to a fair percentage of older patients with AF, with most being under-dosed, the development of a practical prediction model with reliable predictability is of great value. To our knowledge, this will be the first study to establish a feasible prediction model for predicting inappropriate NOAC use in older Chinese patients with AF. In the prediction model of probabilistic estimation, we will combine the above independent predictors and the risk factor variables from previously published research. Accordingly, we believe that the prediction model could be applied as a simpler and more effective tool for clinical decision-making for elderly patients with AF.

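### Model performance is to be judged from one random 80/20 split, with the data used for AUROC selection not stated, no calibration measure, and a comparison method that does not compare models

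*Protocol article*

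**What the plan says.** Under Data separation and feature filtering, the data are to be "randomly divided into training and test sets in a ratio of 8:2", "which will be used for the model establishment and verification, respectively". No third set, cross-validation or bootstrap is mentioned in the article.

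Under Machine learning model establishment, evaluation, and interpretation, eight algorithms are named: logistic regression, random forest, support vector machine, XGBoost, LightGBM, AdaBoost, CatBoost and TabNet. The boosting methods are given as examples, so eight is a minimum. All models are evaluated on five measures: "area under the receiver operating characteristics [AUROC] curve, precision, recall, F1 score, and accuracy". Then: "The acceptably performing machine learning models will be selected according to AUROC". The selected models supply the importance scores and the major predictors.

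Under Statistical analyses: "Interaction analyses will be used to compare predictive performance between machine learning models".

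The Discussion describes the purpose of the model with the phrase "In the prediction model of probabilistic estimation" and says it will be applied in routine clinical practice. Under Primary outcomes, creating the prediction model is the fourth primary outcome.

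**The concern.** Three features of this plan weaken what can be said about the model.

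- **Selection data.** The order of the text is to evaluate all models and then select by AUROC. The only data set named for verification is the test set. Read naturally, the same patients screen the models and supply the reported performance.
- **Calibration.** A tool that gives a patient's probability of inappropriate prescribing can rank patients well and still give wrong probabilities. None of the five measures would show this.
- **Comparison.** An interaction analysis asks whether an effect differs across levels of another variable. It does not estimate the difference in AUROC between two models scored on the same patients.

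At stake is the credibility of a primary deliverable: an imprecise and possibly optimistic AUROC, probabilities that nobody has checked, and a choice between models without a valid measure of their difference.

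**Working it through.** **Inputs.** The article gives no AUROC or precision target for the model, so there is no performance figure to reproduce. From the article: N = 1,500 (Sample size calculation) and the 8:2 split. The test set is 0.2 × 1,500 = 300, if N stays at 1,500; the article allows it to change. No expected rate of inappropriate use is stated in that section. The Discussion cites one cohort with nearly a quarter inappropriate and a Korean study with about 60% label adherence, so about 40% non-adherence. I assume 25% and 40% for the interval, and 20 to 40% in the simulation. AUROC 0.75 is also an assumption.

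**Step 1. Precision of one test-set AUROC.** Hanley–McNeil, with A the AUROC, n1 events and n0 non-events:

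Var = [A(1−A) + (n1−1)(Q1−A²) + (n0−1)(Q2−A²)] / (n1·n0), where Q1 = A/(2−A) and Q2 = 2A²/(1+A).

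For A = 0.75: Q1 = 0.600, Q2 = 0.6429, A² = 0.5625.

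- 25% events (75/225): (0.1875 + 74×0.0375 + 224×0.0804)/16,875 = 0.00124. SE 0.035, half-width 0.069.
- 40% events (120/180): (0.1875 + 119×0.0375 + 179×0.0804)/21,600 = 0.00088. SE 0.030, half-width 0.058.
- All 1,500 at 25% (375/1,125): SE 0.016, half-width 0.031. This is only a guide to what resampling could reach, because it ignores the variability of refitting.

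**Step 2. Optimism if the test set both selects and reports.** Suppose eight models have the same true AUROC and the highest test value is reported. The expected maximum of eight standard normals is 1.42, so

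optimism ≈ 1.42 × √(1−ρ) × SE,

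with ρ the correlation between the models' AUROC estimates. With SE = 0.0352 this gives 0.035, 0.027 and 0.016 for ρ = 0.5, 0.7 and 0.9.

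A simulation checked this: 300 test patients, eight binormal scores, true AUROC 0.70 to 0.80, event rates 20 to 40%, within-class score correlation 0.5 to 0.95, 1,500 runs per setting. The bias of the best of eight was 0.010 to 0.038. At AUROC 0.75 and 25% events it was 0.034, 0.023 and 0.010 for score correlations 0.5, 0.8 and 0.95. For a model fixed before the test set was used, the bias was within 0.002 of zero in every setting.

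**Step 3. Calibration.** AUROC depends only on rank order. Precision, recall, F1 and accuracy depend only on which side of a cut-off each patient falls. If every predicted probability is halved and the cut-off is halved with it, all five measures are unchanged. A patient whose risk is 0.40 would then be told 0.20, and nothing in the plan would reveal it.

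**Step 4. Comparison.** A difference between two AUROCs on the same patients has SE ≈ SE₁ × √(2(1−ρ)) when the two SEs are equal. With SE₁ = 0.0352, the 95% half-width is 0.069 at ρ = 0.5 and 0.031 at ρ = 0.9. The pairing therefore matters, and the named method does not use it.

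**The case against.** A reader might infer that the reported AUROC is certain to be biased upward. The article does not support that. It never says which data yield the AUROC used for selection, and choosing models could belong to the establishment step assigned to the training set. It also screens for acceptably performing models in the plural and does not name a single winner whose AUROC becomes the headline. The best-of-eight figures assume equally good models, which makes the bias largest, and they assume correlations. These objections stand, so the optimism can be claimed only conditionally.

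A reader might also call the single split an error. It is inefficient at this size, but it is a legitimate design. Nor can the article's commitment to a reporting guideline carry the calibration point, because the guideline's content is not in the document.

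It can be said that a condensed article leaves detail to a fuller plan. That is fair for the selection data. It is weaker for the measures, which are counted and listed as five, and for the comparison method, which is named outright. The meaning of interaction analyses is undefined, so this may be loose wording, but as it stands it specifies no valid comparison.

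Finally, Strengths and limitations concedes that the model needs independent validation in other cohorts. That tempers the worry about early use but cures none of the three points. Discrimination and threshold measures do suit the stated aim of identifying patients at risk. They do not suffice for a model that outputs probabilities.

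**Conclusion.** The point holds in this form.

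- **Firm:** the five measures contain no calibration measure for a model described as estimating probabilities and intended for routine use, and the named comparison method does not compare models on the same patients.
- **Firm, given N = 1,500, AUROC 0.75 and 25 to 40% events:** performance would rest on about 300 test patients, with an interval of about ±0.06 to ±0.07.
- **Conditional:** if the test set both selects a best model and reports its AUROC, that figure is too high by roughly 0.01 to 0.04, given near-equal models and the assumed correlations. If selection is confined to the training data, the bias is about 0. The article permits either reading and should exclude the first.

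The possible optimism is smaller than the half-width of the test-set interval, but it always runs upward and can be avoided without new data.

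**What to change.** 1. Add the calibration intercept, slope and curve, and the Brier score, to the measures in the machine learning section.
2. Estimate performance by bootstrap optimism correction or nested cross-validation on all patients, with feature selection and algorithm choice repeated inside the loop. At minimum, state that algorithms are selected by cross-validation within the training set and that the test set is used once, for the final evaluation.
3. In Statistical analyses, replace interaction analyses with a paired bootstrap or DeLong confidence interval for differences in AUROC.

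The cost is more computation, some rewording and a possibly slightly lower reported AUROC. No additional patients or data items are needed.

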### Statistical analyses

Categorical data will be presented as frequencies and be compared by Chi-squared or Fisher's exact test as appropriate. Continuous data will be reported as mean ± standard deviation or median and interquartile range (IQR) and analyzed by either Student's *t*-test or the Mann–Whitney *U* test. In this study, data will be extracted and summarized using Excel 2016. Univariate and multivariate logistic regression analyses will be applied to ascertain the correlation between candidate variables and NOAC inappropriate use. Multicollinearity between the variables will be shifted based on the variance inflation factor (VIF; VIF > 5 is considered strong collinearity) (25). Two criteria will be considered necessary for a variable to be incorporated into the final prediction model: (a) a univariate *p-*value indicative of NOAC prescription inappropriateness ≤0.05 and (b) a plausible connection with risk factors from NOAC inappropriate prescriptions based on previously published research. The risk tendency of inappropriate NOAC use among risk stratifications will be evaluated by the Cochran-Armitage trend test (26). Machine learning algorithms will be built based on the Scikit-learn package (version 0.22.2). Interaction analyses will be used to compare predictive performance between machine learning models. Statistics will be performed employing STATA software (version 12.0, Stata Corporation LLC, College Station, United States), and a *p* < 0.05 will be considered to be statistically significant.

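### Two different entry rules are stated for the final prediction model, and one makes univariate p ≤0.05 a condition that can drop real predictors

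*Protocol article*

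**What the plan says.** The Protocol article describes entry of variables in two places.

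- **Statistical analyses:** "Two criteria will be considered necessary for a variable to be incorporated into the final prediction model". Criterion (a) is a univariate p-"value indicative of NOAC prescription inappropriateness ≤0.05". Criterion (b) is "a plausible connection with risk factors from NOAC inappropriate prescriptions based on previously published research". Both must be met. The same section uses VIF above 5 as its marker of strong collinearity.
- **Data separation and feature filtering:** "Feature selection will be performed using the Sequence Forward Selection algorithm based on RF". The search starts from the empty set and proceeds to "add one variable to the feature subset each time to achieve an optimal performance, which is measured by the F1 score". It uses no p-value and no literature condition.

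Three further statements bear on how these fit together.

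- **Primary outcomes** speaks of one prediction model, built with logistic and machine-learning methods together.
- **Machine learning model establishment, evaluation, and interpretation** says: "Both linear and non-linear machine learning models will be applied to the sets, which include logistic regression, RF, support vector machine". After fitting, "features ranked in the top 50% based on normalized importance scores in selected models will be determined as major predictors".
- The **Discussion** says that "we will combine the above independent predictors and the risk factor variables from previously published research".

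**The concern.** An analyst could follow either entry rule, comply with the article, and arrive at a different set of predictors. The prediction model is one of the declared primary outcomes, and the Discussion intends it for routine clinical use, so the choice should not be left open.

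The univariate condition raises a second problem. A screen on p ≤0.05 tests each variable's marginal association, whereas a multivariable model uses its association given the others. When candidates are correlated, the two can differ in either direction. Table 2 collects overlapping candidates: age, weight, serum creatinine, a Cockcroft-Gault clearance computed from them, and two risk scores that share components. Because the criterion is necessary, a variable that fails it cannot be recovered later.

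**Working it through.** **1. Can the two rules serve different models?** The natural reading would be that the p-value rule governs a logistic model and forward selection governs the machine-learning models. Two statements block this. Logistic regression is listed among the models run in the machine-learning pipeline, and Primary outcomes promises one model from both methods. No section ranks the rules or allocates them.

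**2. What can the univariate screen lose?** The article gives no figure to reproduce, so this is an illustration.

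Inputs:
- Training patients: 0.8 × 1,500 = 1,200 (Sample size calculation; Data separation and feature filtering).
- Event rate: 25%, an assumption close to the rate that the Discussion reports from a cohort of older adults. It is not a design input.
- Two standardised predictors with log-OR 0.25 per SD each and correlation r: assumed.

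Formulas:
- Univariate SE = 1/√(1,200 × 0.25 × 0.75) = 1/√225 = 0.0667.
- Marginal log-OR ≈ 0.25(1 + r).
- Joint SE = 0.0667/√(1 − r²).
- VIF = 1/(1 − r²).
- Power = Φ(z − 1.96).

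| r | Marginal log-OR | Univariate z | Passes screen | Joint z | Significant jointly | VIF |
|---|---|---|---|---|---|---|
| 0 | 0.250 | 3.75 | 96% | 3.75 | 96% | 1.00 |
| −0.5 | 0.125 | 1.88 | 47% | 3.25 | 90% | 1.33 |
| −0.7 | 0.075 | 1.13 | 20% | 2.68 | 76% | 1.96 |

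Same-sign effects with a negative correlation are, after recoding one variable, opposing effects with a positive correlation. That is the pattern masking requires. VIF exceeds 5 only when r² > 0.8, that is |r| > 0.894, so the planned collinearity check would flag none of these rows.

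**3. Check by simulation.** Two binary predictors, each with 40% prevalence; 1,200 patients, 25% events, 500 runs per setting. The predictor of interest has an adjusted OR of 1.6.

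| Correlation (phi) | OR of the other predictor | Passes screen | Significant jointly |
|---|---|---|---|
| 0 | 1.0 | 92% | 92% |
| 0.19 | 0.62 | 80% | 93% |
| 0.33 | 0.50 | 46% | 89% |
| 0.41 | 0.40 | 13% | 86% |
| 0.49 | 0.40 | 6% | 85% |

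The pattern is the same with 1,500 patients and with 40% events.

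**4. The reverse error.** In the same simulation, a predictor with adjusted OR 1.0 passes the screen in 40% of runs (phi 0.33, other OR 2.0) and in 79% (phi 0.41, other OR 2.5). In the joint model it is significant in 5% and 4%.

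**5. Criterion (b).** It is necessary for the prediction model. A factor with no plausible published connection therefore cannot enter, however strongly it is associated in these data. The univariate and multivariate association analysis in the same section is not bound by the criterion and could still report such a factor.

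**The case against.** Several stronger readings are tempting, and the document does not support them.

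- **Age, weight and creatinine clearance mask one another.** A reader might infer this from the Cockcroft-Gault formula. The studies summarised in the Discussion report older age, lower weight and poorer renal function all raising risk. Age and clearance are negatively correlated with effects of opposite sign, so they would reinforce each other: at r = −0.7 the marginal log-OR would be 0.25 + 0.7 × 0.25 = 0.425, z = 0.425/0.0667 ≈ 6.4, and the screen would almost never miss them. One registry there found younger patients among inappropriate dose reductions, but only in comparison with appropriately reduced patients. The masking risk is general and is not shown for these variables.
- **Criterion (b) shuts out hospital factors.** The Introduction cites a source on limited hospital access to NOACs, and Table 2 says availability can affect appropriateness. By the article's own account that factor has support.
- **The risk-factor aim is spoiled.** The entry rule covers only the prediction model.
- **The top-50% cut would label half of all collected variables as major predictors even under pure noise.** The cut comes after feature selection and only in models judged acceptable on AUROC, so that count does not describe the pipeline.
- **The Discussion adds a third rule, a union.** Its wording on combining predictors may simply paraphrase the two criteria, so it is weak evidence.

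It can also be said that a condensed article may leave the allocation of rules to the full protocol. Silence alone would not be a finding. Here, however, the article states both rules, puts logistic regression under the pipeline that uses one of them, and calls the other necessary for the final model. That contradiction stands, as does the weakness of the univariate condition.

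**Conclusion.** The point holds in limited form. The article gives two incompatible entry rules for the final prediction model and no basis for assigning them to separate models. One of them makes univariate p ≤0.05 necessary. That can drop a real predictor masked by a correlated one acting in the opposing direction and can admit a predictor with no effect of its own, and the VIF check does not guard against it.

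In the illustration at r = −0.5 the screen passes the predictor 47% of the time, against 90% significant jointly. Without correlation there is no loss. These figures rest on assumed effects, correlations and event rate; the actual size cannot be found from the document. Criterion (b) restricts the prediction model only.

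A secondary point: the top-50% importance cut has no signal threshold, so the label it gives reflects rank and not strength of evidence.

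**What to change.** 1. Name one selection rule for the final prediction model, and say what the other is for.
2. Remove univariate p ≤0.05 as a condition of entry.
3. Prespecify the candidate list from subject knowledge, including prescriber and hospital factors. Published support can inform the list without being a bar to entry.
4. Fit the candidates together in a penalised logistic model (ridge or elastic net), and repeat any selection step inside each resample.
5. Replace the top-50% cut by importance scores reported with uncertainty intervals.

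Stating which rule applies would by itself resolve the contradiction; steps 2 to 4 deal with the weakness of the screen. The cost is analysis wording and standard software, with no new data. The final model may be less sparse.
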